#### Statistical analysis

The primary analysis approach will be an intention-to-treat (ITT) strategy, including sensitivity analysis for missing data [20], sensitivity analysis for low compliance [21], and sensitivity analysis for use of forbidden rescue medication or potential informative dropout (described in the detailed statistical analysis plan).

For each time-to-event outcome, including the primary outcome, Kaplan–Meier survival curves will be estimated. A Cox stratified proportional hazards regression model, accounting for the randomisation stratifiers in the form of nominal categorical variables, will be used to compare randomised arms and obtain an estimated hazard ratio for the treatment effect with 95% confidence interval. Participant follow-up is on a three-monthly basis, and there will be additional monthly phone calls when participants are able to additionally report on their progress. Days will be the unit of time within the model in order to fully capture the inevitable variation in the time from baseline to monthly contacts and to ascertained outcome events. Each participant who drops out will be included in the analysis and will be assumed not to have the event and be censored at the point of dropout. Time will also be censored for those reaching the 24-month follow-up without an event. Those with an event will not contribute any further time after the event. For the primary outcome, sensitivity analysis will be carried out. This includes an analysis assuming that those who have dropped out for reasons connected with disease severity are alternatively deemed to have had the event and an analysis assuming this alternative for those having experienced two affected joints.

For each binary outcome, a stratified difference in proportions using the Cochran–Mantel–Haenszel method will be used to compare arms accounting for the randomisation stratifiers in their nominal categorical form. For each continuous outcome, including DAS28, differences in the mean of the outcome between arms will be estimated by using a linear mixed effects regression model of the repeated measures of the outcome across follow-up. ‘Visit’ will be included in the model as a continuous covariate with full polynomial terms equivalent to including ‘Visit’ as a categorical factor. Outcome data will be included from the regular visits and from times of measurement, including at ultrasound visits. The model will have a heterogeneous variance first-order autoregressive covariance structure, where measurements at the non-regular visits are included in the variance part of the model at the nearest visit and are included in the mean part of the model in proportion to how the measurement was timed between two visits. The ‘visit’ covariate will be located with an origin at 24 months, so that the model with the interactions of the ‘time’ terms with the other included main effect covariates of study arm, the randomisation stratifiers, and the baseline of the outcome and its missing indicator will directly provide the estimate of the study arm effect and its standard error. The missing indicator method [21] will be used to enable those participants having any outcome data, but with missing baseline data, to contribute to the estimate.

Descriptive statistics will be reported for measures of acceptability, feasibility and safety. Percentage measures will be reported with exact 95% confidence intervals. There is no plan to have stopping rules. It is anticipated that the data monitoring committee (DMC) will request interim data on safety and will advise on further data required for monitoring and on trial statistician blinding status. A detailed statistical analysis plan will be developed from the study protocol prior to the availability of follow-up data for approval by the independent trial steering committee (TSC). The primary analysis will follow the ITT principle; that is, participants will be analysed in the groups to which they were randomly assigned irrespective of treatment received, using all available follow-up data from all randomly assigned participants, with a per-protocol analysis of compliers only, as defined in the statistical analysis plan. Alterations to the statistical analysis plan will require re-approval from the TSC.

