The combination of serum antibodies to citrullinated protein antigens (ACPAs) and joint pain (termed arthralgia), in the absence of clinically detectable synovitis, is considered to most accurately define subjects at high risk of progressing to RA [6–8]. Data from longitudinal observational cohorts indicate that about 40% of high-risk subjects progress to clinically apparent arthritis within 18 months [9]. The combination of IgM rheumatoid factor (RF) and high serum ACPA levels defines those at highest risk; recent unpublished data indicate that the risk of developing disease in subjects with high titre ACPA in the absence of RF may be comparable to that in ACPA^+^RF^+^ subjects [9]. It follows from this that ACPA^+^RF^+^ or ACPA^+^RF^−^ arthralgia individuals would provide a valid target population for therapeutic intervention aimed at prevention of the syndrome we recognise as RA.

Abatacept is a fusion protein composed of the Fc region of the immunoglobulin IgG1 fused to the extracellular domain of cytotoxic T-lymphocyte antigen 4 (CTLA-4) [10]. Specifically, abatacept, a first-in-class co-stimulatory blocker, is a biologic DMARD that targets immune reactions early in the chain of events leading to inflammation in RA. It functions by interrupting the interaction between T cells and antigen-presenting cells, attenuating the co-stimulatory signals required for T-cell activation, differentiation and effector responses [11]. This results in downstream immunomodulatory effects on other inflammatory cells of the immune system.

In patients with established RA, administration of abatacept is associated with statistically significant and clinically meaningful improvements in the signs and symptoms, physical function and health-related quality of life. It inhibits structural damage in a broad spectrum of patients [12, 13], including those with early or established disease [14] and those with an inadequate response to tumour necrosis factor (TNF) blockade [15]. Interestingly, disease activity scores (DASs) have been shown to continue to improve beyond 12 months, indicating that the beneficial effects of co-stimulatory blockade not only are sustained but accumulate over extended periods of time.

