### Eligibility criteria

#### Inclusion criteria

Male or female subjects who are at least 18 years old.Arthralgia, defined as non-traumatic joint pain localised to synovial joints, including (but not necessarily confined to) hands, wrists or feet and considered (by the supervising rheumatologist) to be inflammatory in nature.Positive for serum RF and ACPA as defined by local clinical laboratory testing. Subjects who are RF-negative but who carry high levels of serum ACPA (defined as being at least 3 × upper limit of normal [ULN] for the assay) may be included.Able and willing to give written informed consent and comply with the requirements of the study protocol (Additional file 1).

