### Statistical considerations

#### Randomisation procedure, blinding and data management

If the participant is willing to participate in the trial, informed consent will be obtained at the start of the screening visit (Additional files 1 and 2). Screening assessment data will be entered by sites onto a web-based InferMed MACRO Electronic Data Capture (EDC) system hosted on a dedicated secure website by King’s College London, using only the participant’s initials and date of birth as identifiers (Additional file 3). The EDC system will automatically assign a unique participant identification number (PIN) to each participant as they are registered onto the EDC system. Participants who consent to screening but who are subsequently found to be ineligible will also be recorded in the EDC system for CONSORT (Consolidated Standards of Reporting Trials) reporting purposes. These procedures will operate in accordance with the International Conference on Harmonisation of Technical Requirements for Registration of Pharmaceuticals for Human Use guidelines for good clinical practice (GCP), meeting the requirements of the Medicines and Healthcare products Regulatory Agency.

Once participants are confirmed eligible, authorised study site staff will access the web-based randomisation system and enter the PIN, initials and date of birth of the participant along with details of any characteristics to be used in the randomisation algorithm. Staff at individual centres and the sponsor will be unaware of the allocation sequence.

Participants will be randomly assigned to IMP (abatacept) and placebo groups by using the method of stratified randomisation with randomly permuted blocks within strata defined by gender, country (UK and the Netherlands) and smoking status (never, previous and current). Once the participant is randomly assigned, the system will automatically recognise what active and placebo kit numbers are available in the site pharmacy and will select four blinded treatment kit numbers from the appropriate trial arm and this will be allocated to the participant. At each follow-up visit, site staff will again access the randomisation system and allocate new treatment kits for the participant. All participants and staff involved in the conduct of the study will be blind to treatment allocation throughout the trial.

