#### Sample size

Using time to development of arthritis as the primary outcome, or development of RA within 24 months of follow-up, according to 2010 ACR/EULAR criteria, a total of 52 study subjects need to present with this endpoint from 206 randomly assigned, based on the following information. It is conservatively anticipated that 40% of participants on placebo will develop arthritis. A sample size of 172 subjects would be needed to provide 80% power to detect a 50% relative reduction to 20% in the abatacept arm (a hazard ratio of 0.437) on the basis of a two-sided log-rank test at the 5% level of significance without loss to follow-up of any of the required 52 events. Therefore, 206 subjects (103 per arm) will be randomly assigned to allow for loss of events due to dropout, applying a conservative 20% inflation for dropout.

Similar effect sizes are detectable for binary outcomes and for other time-to-event and proportion outcomes such as the development of RA according to ACR/EULAR 2010 criteria alone. For continuous secondary outcomes, such as DAS measures, a medium effect size difference in means (of size 0.5 of a standard deviation, or SD) between the arms, based on the two-sided unpaired *t* test at the 5% significance level, can be detected with 85% to 90% power if 146 to 172 subjects are followed up. In view of the number of required secondary outcomes, with 172 participants followed up, there is also 80% power to detect medium-sized effects in secondary outcomes (0.52 of a SD) using a secondly applied significance level of 1%. Analyses incorporating baseline adjustment or repeated measures data (or both) will provide increased precision.

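### The primary Cox model could cheaply include baseline RF/ACPA status, a risk marker the protocol names and must determine for entry; the expected gain is small and the plan is not wrong without it

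*Protocol article*

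**What the plan says.** Under Randomisation procedure, blinding and data management, permuted blocks are used within "strata defined by gender, country (UK and the Netherlands) and smoking status (never, previous and current"). This gives 2 x 2 x 3 = 12 strata. Under Statistical analysis, the primary time-to-event model is a stratified Cox regression "accounting for the randomisation stratifiers in the form of nominal categorical variables". Whether the stratifiers enter as strata or as covariates, no further baseline variable is named.

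Serology appears elsewhere as a marker of risk and as a condition of entry. The Background states: "The combination of IgM rheumatoid factor (RF) and high serum ACPA levels defines those at highest risk". The Inclusion criteria ask for positive RF and ACPA on local laboratory testing and add an exception: "Subjects who are RF-negative but who carry high levels of serum ACPA", meaning at least 3 times the upper limit of normal (ULN), may also enter. Three serological groups can therefore be enrolled:

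- RF-positive with ACPA at least 3 x ULN
- RF-positive with lower positive ACPA
- RF-negative with ACPA at least 3 x ULN

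**The concern.** The Background links serology to the risk of the very event that is the primary endpoint, and gives no such risk rationale for gender, country or smoking. The Sample size section itself says that baseline adjustment improves precision, and the continuous outcomes are adjusted for their baseline values. The primary endpoint has no disease-related baseline covariate.

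Two things could be at stake. Leaving out a prognostic variable pulls a Cox hazard ratio slightly towards 1 and costs some power. And with about 52 events, a chance difference in serostatus between the arms would shift the estimate. An adjustment added only after such a difference had been seen would carry little weight.

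**Working it through.** **1. The plan's own figures.** The inputs come from Sample size: "It is conservatively anticipated that 40% of participants on placebo will develop arthritis"; a "50% relative reduction to 20% in the abatacept arm (a hazard ratio of 0.437"); the calculation is made "on the basis of a two-sided log-rank test at the 5% level of significance"; "A sample size of 172 subjects would be needed to provide 80% power".

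- Hazard ratio = ln(0.8)/ln(0.6) = 0.437, as stated.
- Events (Freedman) = (1.96 + 0.84)² x [(1 + 0.437)/(1 - 0.437)]² = 51.1, rounded up to 52, as stated.
- Subjects = 51.1/0.30 = 170.3, or 172 when each arm is rounded up to 86, as stated.

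**2. Power with and without serostatus.** The article gives no hazard ratio for serostatus and no group shares, so both are assumed here. Set-up: n = 172, 1:1, exponential event times, placebo 24-month risk held at 40%, conditional treatment hazard ratio 0.437, no dropout, the 12 design strata not modelled. Shares are 50/25/25% for RF+/high ACPA, RF+/lower ACPA and RF-/high ACPA. There were 4,000 replicates per row for power and 3,000 for type I error.

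| Serogroup hazard ratios (RF+/high : RF+/lower : RF-/high) | Power without | Power with | Type I error without / with | Estimated treatment HR without / with |
|---|---|---|---|---|
| 1 : 1 : 1 | 82.2% | 82.5% | 3.9% / 4.0% | 0.432 / 0.430 |
| 2 : 1 : 2 | 81.1% | 81.7% | 4.4% / 4.6% | 0.434 / 0.428 |
| 2 : 1 : 1.5 | 81.9% | 82.8% | 5.0% / 5.1% | 0.435 / 0.429 |
| 3 : 1 : 3 | 80.3% | 81.3% | 4.6% / 4.9% | 0.438 / 0.429 |
| 3 : 1 : 1.5 | 80.0% | 82.4% | 4.8% / 4.8% | 0.445 / 0.431 |
| 4 : 1 : 2 | 78.9% | 81.4% | 5.2% / 5.2% | 0.449 / 0.433 |

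The Monte Carlo standard error of each power figure is about 0.6 points. The gain is near zero when risks are equal, about 1 point at hazard ratios of 2, and about 2 points in the steepest rows.

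A two-level serostatus term gives a similar picture (3,000 replicates per cell). The gain is about 0 to 1 point up to a hazard ratio of 2. The largest gain is at a hazard ratio of 3 with an even split: 78.9% to 82.5%, or 3.6 points.

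**3. Chance imbalance.** Take 103 per arm and a marker with an assumed prevalence of 60%.

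- SD of the arm difference = sqrt(2 x 0.6 x 0.4/103) = 0.068.
- P(difference over 10 points) = P(|Z| > 0.10/0.068), about 14%. For a minority share of 20% to 50% it is 7% to 15%.
- Shift in the log hazard ratio at an assumed marker hazard ratio of 2: 0.10 x ln 2 = 0.069, a factor of 1.07 or 0.93. At a hazard ratio of 3 it is 0.10 x ln 3 = 0.110, a factor of 1.12.
- Standard error of the log hazard ratio with 52 events: about 2/sqrt(52) = 0.277. The shift at a hazard ratio of 2 is 0.069/0.277 = 0.25 standard errors.
- A result at z = 1.96 would become 1.71 or 2.21 (p about 0.09 or 0.03). Only a borderline result would be affected.

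**The case against.** The strongest reply is that the plan does something standard. Adjusting for the variables used in randomisation follows the design, and nothing in the Statistical analysis section is contradicted by leaving serology out. That stands.

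A reader might infer from the Background that serostatus is the main driver of risk among those enrolled. The article does not say so. The same sentence goes on to report, from unpublished data, that RF-negative people with high ACPA may have a risk similar to that of people positive for both. Eligibility removes much of the contrast. Some gradient may still remain: the 3 x ULN threshold applies only to RF-negative subjects, so RF-positive people with lower ACPA can enter, while the Background places the highest risk in RF with high ACPA.

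A reader might also infer that the omission biases the comparison or inflates type I error. It does neither: the simulated error rate is near 5% with or without the term, and random imbalance is already part of the sampling error that the test and interval allow for.

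A larger power gain can be produced by treating RF and ACPA level as two independent binary factors, each at 60% prevalence with a hazard ratio of 2: power then goes from 82% to 86%. But 0.4 x 0.4 = 16% of such a population would be RF-negative with lower ACPA, a group the Inclusion criteria do not admit.

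Two further objections stand in part. A supportive adjusted analysis may exist in the detailed statistical analysis plan, which is not shown, so it cannot be said that nothing addresses the point; what can be said is that the primary model is written out in the article without serostatus. And serology is measured locally across 31 clinics, so multiples of the ULN may not be fully comparable between assays, and the article does not say that the multiple is recorded for RF-positive subjects.

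**Conclusion.** The point holds as a modest recommendation. The named primary model uses gender, country and smoking and leaves out a baseline marker that the protocol itself links to risk and must determine for every participant. The primary analysis is valid as written. Adjustment would add about 0 to 2 points of power under assumed serogroup hazard ratios of 1 to 4 and the assumed 50/25/25% shares. It would also remove a possible shift of about 7% in the hazard ratio for a 10-point imbalance at an assumed marker hazard ratio of 2. If the serogroups have equal risk, which the Background leaves open for two of the three, there is almost no gain and almost no loss. The case for acting rests on low cost and on the need to fix the covariate in advance, not on a large expected benefit.

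**What to change.** Before unblinding, pre-specify baseline serostatus as a covariate in the primary Cox model alongside the stratifiers. Use three levels: RF-positive with ACPA at least 3 x ULN, RF-positive with lower ACPA, and RF-negative with ACPA at least 3 x ULN, each relative to the local assay's ULN. If the ACPA multiple was not recorded for RF-positive participants, use RF status alone. Keep the stratifier-only model as a sensitivity analysis.

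Stratification itself can no longer change, since recruitment closed at the end of December 2018 (Trial status). The model could still be fixed, as 24-month follow-up of the last participants runs to about the end of 2020. The Statistical analysis section allows changes to the analysis plan with re-approval by the trial steering committee.

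The cost is 1 to 2 degrees of freedom against about 52 events, some noise from differing local assays, and one committee approval. The adjusted hazard ratio is conditional on serostatus and can lie slightly further from 1 than the stratifier-only one (0.433 against 0.449 in the steepest scenario above), so the report should state which is primary.

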In view of the large number of secondary outcomes and the fact that the sample size was not set to detect powered effects specifically on the scale of these secondary measures, the use of a 1% level of significance goes only partway towards addressing the fact that multiple testing increases the chance that significant secondary findings are false. The results from secondary outcome analyses will be interpreted cautiously and in relation to the estimated confidence limits on the actual scale of the measures. Significance tests will be used sparingly and restricted where possible to address the stated hypotheses. Results that are significant in isolation will be interpreted less strongly than the set of results that are mutually supportive or that support the corresponding primary outcome or that are supported in previous research findings.

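### Secondary time-to-event outcomes have a 1% significance level but a 95% interval, so the interval can exclude a hazard ratio of 1 when the 1% test is not met

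*Protocol article*

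**What the plan says.** Three statements in the Statistical considerations part of the protocol article bear on this.

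- **Level for secondary outcomes (Sample size).** With 172 participants followed up, the article claims "80% power to detect medium-sized effects in secondary outcomes (0.52 of a SD) using a secondly applied significance level of 1" per cent. The reason given is multiplicity, with the admission that "the use of a 1% level of significance goes only partway towards addressing the fact that multiple testing increases the chance" of false findings.
- **How secondary results will be read (Sample size).** They will be "interpreted cautiously and in relation to the estimated confidence limits on the actual scale of the measures".
- **Interval level (Statistical analysis).** The paragraph on survival methods opens "For each time-to-event outcome, including the primary outcome, Kaplan–Meier survival curves will be estimated". It goes on to a stratified Cox model that will be used to "obtain an estimated hazard ratio for the treatment effect with 95% confidence interval". No separate level is given for secondary outcomes.

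The Secondary endpoints section lists one outcome that is plainly time-to-event: time to starting DMARD treatment. Development of RA may be a second, because the Sample size section names RA by the ACR/EULAR criteria alone when it speaks of further time-to-event and proportion outcomes.

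The primary outcome is designed on a "two-sided log-rank test at the 5% level of significance", so a 95% interval is right there.

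**The concern.** A 95% interval corresponds to a two-sided 5% test. If significance for a secondary hazard ratio is judged at 1%, the matching interval is 99%. As written, the article gives two readings of one result. A p-value between 0.01 and 0.05 is not significant at the 1% level, yet the printed interval excludes no effect. Because the article tells the reader to look at the confidence limits, the interval is what many will go by. Reading it that way brings back a 5% criterion for these outcomes, which is looser than the level adopted for multiplicity. No statement says which of the two readings governs.

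**Working it through.** **1. The article's own figures.**

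- Power at 1%: 172 followed up is 86 per arm, with a difference of 0.52 SD. The normal approximation gives Φ(0.52 × √(86/2) − 2.576) = Φ(3.410 − 2.576) = 0.798. The noncentral t gives 0.788. The stated 80% is reproduced.
- Design hazard ratio: ln(0.8)/ln(0.6) = 0.437, as stated.
- Events by Freedman's formula: (1.960 + 0.842)² × (1.437/0.563)² = 51.1, rounded up to 52, as stated.

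The figures are sound. The mismatch is only between the two stated levels.

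**2. Interval against test under no effect.** The 95% interval uses 1.960 standard errors, and a two-sided 1% test needs 2.576. Per outcome, the 95% interval excludes 1 with probability 5%, and the 1% test rejects with probability 1%. For two independent outcomes the expected numbers are 2 × 0.05 = 0.10 and 2 × 0.01 = 0.02. The chance of at least one is 1 − 0.95² = 9.8% against 1 − 0.99² = 2.0%.

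**3. Hazard ratios on which the two disagree.** Take SE(ln HR) = 2/√events. The article gives no event count for secondary outcomes, so the counts here are assumptions: 52 (the primary design figure), 40 and 30. The limits are exp(−1.960 × SE) for the 95% interval and exp(−2.576 × SE) for the 1% test.

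| Assumed events | 95% interval excludes 1 below HR | 1% test met below HR | Chance of landing between, if true HR is 0.437 |
|---|---|---|---|
| 52 | 0.581 | 0.489 | 19% |
| 40 | 0.538 | 0.443 | 23% |
| 30 | 0.489 | 0.390 | 24% |

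The last column is Φ(m − 1.960) − Φ(m − 2.576), with m = |ln 0.437|/SE. For 52 events, m = 0.828/0.277 = 2.985, which gives 0.847 − 0.659 = 0.189.

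**4. Example.** With 52 events and an observed hazard ratio of 0.52, p = 0.018. The 95% interval is 0.30 to 0.90 and excludes 1. The 99% interval is 0.25 to 1.06 and includes it.

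**5. Width of the matching interval.** 2.576/1.960 = 1.31 times as wide on the log hazard scale.

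The match between interval and test is exact when both come from the same Cox model by the Wald method, and close for a log-rank p-value.

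**The case against.** **The 1% level may sit beside 5% and not replace it.** The Sample size section first powers continuous secondary outcomes at 5%, then adds the 1% figure, described as "using a secondly applied significance level of 1" per cent. Its remark on other time-to-event outcomes follows the 5% calculation, and the 1% power figure is in SD units. This stands as an ambiguity. The later text on multiplicity refers to the 1% level for secondary outcomes in general, so the mismatch remains, and the article does not say which level decides.

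**Confidence limits can be read for size and precision only.** The phrase about the actual scale of the measures supports this, and nothing in the article declares significance from an interval. A 95% interval beside a stricter test level can be coherent if the reader is told that this is intended. The article does not say so.

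**Reporting detail belongs in the analysis plan, which is not shown.** That would answer a complaint that something is missing. Here the article states both levels, and it says the analysis plan is developed from the protocol, so the mismatch can carry over.

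Two stronger readings are tempting but unsupported:

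- A reader might infer that protection against multiplicity is lost. It is not. The Sample size section also promises cautious interpretation, sparing use of tests, and less weight for isolated significant results than for mutually supportive ones.
- A reader might multiply over the whole secondary list. With about 21 measures taken as independent, 1 − 0.95²¹ = 66% against 1 − 0.99²¹ = 19%. The article does not support this. It fixes no interval level for the Cochran–Mantel–Haenszel or mixed-model comparisons. The list includes adverse events, for which safety reporting is descriptive, and a questionnaire on trial participation scheduled only at screening. Related indices such as DAS28, SDAI and CDAI are not independent.

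**Conclusion.** The point holds as a minor inconsistency. For one or two secondary time-to-event outcomes, the stated 95% interval does not match the stated 1% level. The firm size is 5% against 1% per outcome under no effect. The range of hazard ratios in dispute, about 0.49 to 0.58, assumes 52 events and the usual large-sample standard error; it shifts downward with fewer events. The 19% to 24% chance of a conflicting result further assumes a true hazard ratio of 0.437 for the secondary outcome, which the article does not claim. The primary analysis, its 95% interval and the sample size are unaffected.

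**What to change.** In the analysis plan, and in the protocol text if it is amended:

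- Keep the 95% interval for the primary hazard ratio.
- For secondary hazard ratios, report 99% intervals, either alone or beside the 95% intervals, and state that the 1% level governs claims of significance. If both are shown, label the 95% interval as descriptive.
- Use the same level for the binary and continuous secondary outcomes, whose interval level the article leaves open.

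This is a wording change with no new data or analysis. The Statistical analysis section requires the trial steering committee to re-approve alterations to the analysis plan, so it should be settled before secondary results by arm are seen. The one drawback is that 99% intervals are 1.31 times as wide (on the log scale for hazard ratios), so secondary estimates will look less precise.

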#### Unscheduled visit assessments

These assessments will be undertaken for subjects experiencing worsening of symptoms or swelling of joints between scheduled visits. Study subjects will be seen promptly and usually within two weeks of new signs and symptoms developing.Physical examinationDisease activity (includes extended joint counts 68/66, DAS28, simple disease activity index (SDAI), clinical disease activity index (CDAI), pain visual analogue scale (VAS) and physician and patient global assessments (VAS))ACR/European League Against Rheumatism (ACR/EULAR) remission (as defined in [18])Acute-phase reactants: erythrocyte sedimentation rate (ESR) and C-reactive proteinPatient questionnaires as listed above at baseline visitConfirmation of clinically apparent synovitis by ultrasonographyBlood for biomarkers (this will replace the subsequent scheduled blood draw when the date of the unscheduled visit precedes the next scheduled visit by not more than four weeks)Urine for biomarkers (this will replace the subsequent scheduled urine collection when the date of the unscheduled visit precedes the next scheduled visit by not more than four weeks).

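### The model for continuous secondary outcomes breaks down when a scheduled and an off-schedule record share a nearest visit, and its polynomial misplaces off-schedule records near the ends of follow-up

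*Protocol article*

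**What the plan says.** The Statistical analysis section of the protocol article gives one model for every continuous outcome, a "linear mixed effects regression model of the repeated measures of the outcome across follow-up". Four of its statements matter here.

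- **Data:** "Outcome data will be included from the regular visits and from times of measurement, including at ultrasound visits".
- **Covariance:** "The model will have a heterogeneous variance first-order autoregressive covariance structure". Off-schedule records enter it by this rule: "measurements at the non-regular visits are included in the variance part of the model at the nearest visit".
- **Mean:** visit "will be included in the model as a continuous covariate with full polynomial terms equivalent to including" visit as a categorical factor, and off-schedule records "are included in the mean part of the model in proportion to how the measurement was timed between two visits".
- **Estimate:** the time origin is set at 24 months, so that the arm term is the 24-month difference.

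The Unscheduled visit assessments section says when extra visits occur: "These assessments will be undertaken for subjects experiencing worsening of symptoms or swelling of joints between scheduled visits". DAS28, SDAI, CDAI, pain and the questionnaires are all recorded there. Only the blood and urine biomarker samples may stand in for the next scheduled collection, and only when the extra visit falls within four weeks before it. The section on treatment after the primary endpoint keeps participants on the full visit schedule.

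**The concern.** The rule for the covariance lets one participant hold two records at the same visit index, and an autoregressive structure treats such records as perfectly correlated. The trial's own visit rules make such pairs likely. Scheduled visits are 13 weeks apart, so an extra visit after the first half-interval lies within 13/2 = 6.5 weeks of a scheduled follow-up visit, and that visit's clinical assessment still takes place.

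The rule for the mean joins a saturated polynomial to placement by timing. A saturated polynomial matches a categorical visit factor only at the scheduled times. Between them it need not behave like an interpolation between neighbours.

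Extra visits are also prompted by worsening, so pooling them with scheduled visits could pull fitted means towards flare values. At stake is whether the main analysis of DAS28, HAQ and the other continuous outcomes can be run and reproduced from what is written.

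**Working it through.** **Plan's own figures.** The article gives no figure for this model. Its power statements for continuous outcomes (Sample size) reproduce by noncentral t: 0.5 SD at 5% gives 85.1% with 146 participants and 90.3% with 172; 0.52 SD at 1% with 172 gives 78.8% (79.8% by normal approximation), against the stated 85% to 90% and 80%. They are not in question.

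**1. Covariance.** Under ARH(1), cov(i, j) = s_i · s_j · ρ^|i−j|. Take eight follow-up visits (weeks 13 to 104, Table 1) and one extra record whose nearest visit is k.

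- The scheduled and extra records at k each have variance s_k².
- Their covariance is s_k² · ρ⁰ = s_k², so their correlation is 1.
- The 2×2 block has determinant s_k⁴ − s_k⁴ = 0.
- Each has covariance s_k · s_j · ρ^|k−j| with any other visit j, so two rows of the 9×9 matrix are identical and its rank is 8.

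This holds for any ρ and any SDs. Numerically, ρ = 0.3, 0.6 and 0.9 each give rank 8 of 9. With assumed ρ = 0.6 and SDs from 1.0 to 1.5, the eight scheduled visits alone have rank 8 of 8 and determinant 1.39. Adding the extra record gives a smallest eigenvalue of about 1e-16. An assumed residual variance of 0.3 on the diagonal raises it to 0.30, and the model becomes estimable.

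**2. Mean.** With eight follow-up visits the saturated polynomial has degree 7. At fractional visit t, its fitted value is the sum of w_k × (mean at visit k), with w_k = ∏_{m≠k} (t − m)/(k − m). Midway between weeks 91 and 104, t = 7.5:

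- w_8 = (6.5 × 5.5 × 4.5 × 3.5 × 2.5 × 1.5 × 0.5)/5040 = 1055.74/5040 = 0.209
- w_7 = (6.5 × 5.5 × 4.5 × 3.5 × 2.5 × 1.5 × 0.5)/720 = 1055.74/720 = 1.466

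| Week | 13 | 26 | 39 | 52 | 65 | 78 | 91 | 104 |
|---|---|---|---|---|---|---|---|---|
| Weight | 0.016 | −0.133 | 0.489 | −1.047 | 1.466 | −1.466 | 1.466 | 0.209 |

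Linear placement would give 0.5 and 0.5 on weeks 91 and 104. The absolute weights sum to 6.3. Midway between weeks 13 and 26 the pattern is the mirror image. Midway between baseline and week 13 the curve extrapolates, because baseline is a covariate in this model, and the absolute weights sum to 59.5. Mid-follow-up (t = 4.5) the two neighbours get 0.60 each and the absolute weights sum to 1.5.

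Outcomes with four follow-up visits in Table 1 (EQ-5D, FACIT-F, RA-WIS, illness perception) need only degree 3. Midway between the last two visits the weights are 0.06, −0.31, 0.94 and 0.31, which is far milder.

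The polynomial design itself is full rank (8 of 8), though poorly conditioned (condition number 5.3e7 in visit units).

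**3. Symptom-triggered timing.** No document gives a rate of unscheduled visits, so size can only be shown under assumptions. All runs added a residual variance so that the model could be fitted.

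- *Triggering by the outcome value, 86 per arm, total SD 1, true difference −0.5, about 0.4 to 1.8 extra visits per placebo participant.* Compared with scheduled visits only, the 24-month difference moved by at most 0.004 SD with the polynomial and 0.02 SD with linear interpolation, against a standard error of about 0.15 to 0.16. The average over visits moved by 0.006 to 0.03 SD. With no true effect there was no shift at 24 months.
- *Triggering in 15% (placebo) versus 5% (abatacept) of 13-week intervals, with a 1 SD flare and no other arm difference.* Shifts reached about 0.10 to 0.13 SD at intermediate visits and were near zero at 24 months.
- *A further run with assumed trigger rates.* It gave about 0.01 SD at 24 months, against a standard error of about 0.16, and 0.02 to 0.10 SD at most intermediate visits.

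**The case against.** The strongest reply is that the term mixed-effects model may imply ARH(1) random effects plus a residual. That model can be fitted, and a residual term or a rule for duplicate records is ordinary content for the statistical analysis plan, which is not shown. This stands in part: a reader might infer that the model cannot be fitted at all, and the article does not support that. Singularity needs both the literal reading and a shared visit index. But the article goes beyond leaving detail open. It fixes the covariance type and the nearest-visit rule, and together these fail on the literal reading for data that the visit rules will produce.

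On the mean, placement by timing may simply mean entering a fractional visit value into the polynomial; the text does not mention linear interpolation. So the two statements need not be a formal contradiction. The behaviour of the fitted curve near the ends remains, and a record there is not placed proportionately between its neighbours in any useful sense.

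On bias, the plan's estimate is at 24 months, where every run puts the shift near zero. The 15% versus 5% scenario gives placebo three times as many flares, so part of that difference may be real disease difference. Not all off-schedule data are symptom-triggered either: routine scans may fall up to two weeks from the scheduled visit. These points stand.

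Finally, dropping off-schedule records discards observed values, possibly including some recorded just before dropout. That is a fair cost of the simpler remedy.

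**Conclusion.** The point holds as a moderate defect confined to continuous secondary outcomes. With ARH(1) as the only within-person covariance, any participant with a scheduled and an off-schedule record nearest the same visit makes the covariance matrix singular, whatever the parameters. The likelihood is then undefined unless a residual variance, which the section does not state, is added. For outcomes with eight follow-up visits, the degree-7 polynomial misplaces off-schedule records near the ends of follow-up; the effect is small mid-follow-up and milder with four follow-up visits.

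Two stronger readings are not supported. A reader might infer that the polynomial is singular too; it is not. A reader might also infer material bias in the secondary results. A shift in intermediate-visit contrasts is possible, but its size rests on trigger rates that the documents do not give, and it is near zero at 24 months. The primary Cox analysis does not use this model.

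**What to change.** Preferred: make the main model one record per participant per scheduled visit window, with visit as a categorical factor, and move off-schedule records to a labelled sensitivity analysis.

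If off-schedule records stay in the main model, then:

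- state a residual variance in addition to ARH(1), or a continuous-time correlation on actual dates;
- place these records by linear interpolation between adjacent visit means;
- add a scheduled-visits-only sensitivity analysis.

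Either option is a wording change to the analysis plan, with the steering-committee re-approval that the article already requires for alterations. The small downside of the first option is that some observed off-schedule values leave the main secondary model.
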